**4- Experimental plan**

***Choice of the experimental plan and justification***

It is a single-center, randomized, open-type N-of-1 trial (cross-over test series randomized in unique individuals). This is an open study since the techniques cannot be blinded ; however the endpoint chosen is objective (clotting or non-clotting of the dialysis circuit), and not amenable to interpretation. Moreover, the patient is not necessary blinded because this should not influence the response. The choice of N of 1 trial is justified because it is important to choose the best technique according to the patient, and the experimental design can provide an individual response and assess the repeatability of the response by the same technique in the same patient. This experimental design is made possible due to the completion of three dialysis sessions per week chronically ineffective a dialysis session to the next session with a rapid assessment (the same day as the dialysis session) of the test main judgment and fact will be selected patients with contra-indication for LMWH for at least 3 consecutive dialysis sessions without heparin. In addition, this experimental design allows techniques comparison across treatment groups.

The unit of randomization will be patient and will be made according to the following scheme:

- A = discontinuous rinses, B = dilution and C = adsorbed heparin
- The 6 possibles sequences of treatments are:
  - ABC
  - ACB
  - BAC
  - BCA
  - CAB
  - CBA

The patient will be randomized into one of six arms and make sure to have a number of patients included multiple of 6 (see calculation of the number of subjects required). Randomization will be by random blocks of varying size. The order of the types of sessions vary all three triplets for the same patient if the dialysis without heparin must be repeated beyond the first triplets. As a patient may contribute to several sequences, the patient will be considered as a cluster randomization.

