***Selection criteria for patients***

Inclusion criteria:

- Patients (male or female) older than 18 years

- Hemodialysis due to chronic end stage renal disease

- Contraindications to the use of LMWH in hemodialysis, planned for at least three consecutive sessions because of:

o high risk of bleeding

• active bleeding, whatever the origin

• recent surgery or puncture body (<15 days)

• curative treatment with unfractionated heparin or anti-vitamin K.

o uremic pericarditis

o disease cholesterol emboli

o thrombocytopenia heparin

- Informed Consent signed

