**5- Design and conduct of research**

***Follow-up***

Each dialysis session includes a medical examination and a nurse monitoring. The information session is recorded in the case report form, some data are automatically transmitted by the generator to the dialysis Sined Medware ® software and recorded in the secure medical file of the patient. The estimated dialysability urea by the generator induces no extra cost.

Information contained in the protocol specification

At the beginning of the session

• weight, blood pressure, heart rate

• since the last session : weight gain and symptoms occurred

Monitoring of the dialysis session

• Continuous (Sined Medware ® Software generator Hospal Integra ®: blood flow, venous pressure, ultrafiltration rate, urea dialysance)

• every 30 ': blood pressure, heart rate.

• incidents during the session: clotting of the circuit (partial / full), clinical symptoms.

At the end of the session: session duration, weight, total urea dialysance

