**6- Procedures evaluated**

**For all patients :**

- 3 hemodialysis sessions of 4 hours per week

- vascular access : arteriovenous fistula (mono or biponction with 15 G needles) or dual lumen central catheter

- blood flow : 250 to 300 ml / min

- dialysate : flow 500 ml / min, sodium conductivity 14.4 mS / cm ; bicarbonate conductivity 3.3 mS / cm, temperature 36 °C

- Dialysis membrane : AN 69 ST (NEPHRAL 400 ST)

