***Secondary endpoints***

1. Loss of dialysis efficiency

- Urea dialysance during the session (online measurement)
- hyperhydratation (weight at the end of the session: + 0,500 kg over the dry weight)

1. Dialysis session tolerance

- clinical secondary effects (headache, cramps, symptomatic arterial hypotension)
- any bleeding in the 48 heures following the dialysis session

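### The bleeding endpoint's 48-hour post-session window leaves out the session itself and, if sessions are on alternate days, takes in the next session, usually under another technique

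*Protocol*

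**What the plan says.** Section 7 of the protocol lists two tolerance endpoints. One is "any bleeding in the 48 heures following the dialysis session". The other is "clinical secondary effects (headache, cramps, symptomatic arterial hypotension"), which does not include bleeding. No other endpoint covers bleeding.

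Section 6 gives every patient "3 hemodialysis sessions of 4 hours per week" and does not say on which days or at what hours. Section 4 introduces the randomised orders with "The 6 possibles sequences of treatments are" and lists all six orders of A (rinses), B (dilution) and C (adsorbed heparin). For patients who need more than one triplet it adds: "The order of the types of sessions vary all three triplets for the same patient". Among the inclusion reasons in section 4 is "active bleeding, whatever the origin".

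Section 5, Follow-up, records at the start of each session "since the last session : weight gain and symptoms occurred", and during it "incidents during the session: clotting of the circuit (partial / full), clinical symptoms". Neither item names bleeding.

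**The concern.** The techniques change from one session to the next, so a session-level safety endpoint needs a window that contains the exposure and stops before the next exposure begins. Taken literally, this window may fail on both counts.

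The session itself matters here. Technique C rinses the membrane with heparinised saline before dialysis, in patients selected for a contraindication to heparin. For another regional heparin method, the protocol's Introduction cites bleeding complications during sessions. Comparing the safety of the three techniques is a stated secondary objective (section 3). If bleeding during dialysis is left out or counted for the neighbouring technique, that comparison loses contrast. Bleeding that was already active at entry adds events that no technique caused.

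**Working it through.** The plan has no calculated figure to reproduce here; the 48 hours is a definition. The check is a timeline.

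**Inputs.** Session length 4 h, three per week (section 6). Window 48 h from the end of the session (section 7). Start-to-start gap *g*: not stated, so assumed and varied.

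**Formula.** Put the start of session *n* at 0 h. The session runs from 0 to 4 h and the window from 4 to 4 + 48 = 52 h. Session *n*+1 runs from *g* to *g* + 4. Overlap = max(0, min(52, *g* + 4) − *g*).

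| Assumed gaps (h) | Overlap, window counted from session end (h) | Overlap, window counted from session start (h) |
|---|---|---|
| 48 / 48 / 72 | 4 / 4 / 0 | 0 / 0 / 0 |
| 46 / 50 / 72 | 4 / 2 / 0 | 2 / 0 / 0 |
| 56 / 56 / 56 | 0 / 0 / 0 | 0 / 0 / 0 |

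For *g* = 48: min(52, 52) − 48 = 4 h, the whole next session. For *g* = 50: min(52, 54) − 50 = 2 h. For *g* = 72 or 56 the window has closed before the next session starts.

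**The session's own 4 hours.** Counted from the end, the window covers 0 of these 4 hours, whatever the spacing.

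**Which technique is next.** Within a triplet, the next technique differs in 6 of 6 orders. Between triplets, if orders are independent, the last technique of one equals the first of the next in 12 of 36 pairs (1/3). If the next order must differ, it is 12 of 30 (0.40). If an order is simply repeated, it never happens.

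**Share of sessions whose window covers a session under another technique, at 48/48/72 h, in an unbroken run of triplets:**

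- Triplets match calendar weeks: (1 + 1 + 0)/3 = 67%.
- Triplets start mid-week, independent orders: one short gap now falls between triplets, so (1 + 2/3 + 0)/3 = 56%.
- Mid-week, next order forced to differ: (1 + 0.60 + 0)/3 = 53%.

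A patient with a single triplet started mid-week has only one short gap inside it, so the share is 1 of 3.

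**What happens to a bleed during dialysis, read literally.** After a 48-hour gap it counts for the preceding session's technique. After the 72-hour gap it falls in no window, because the preceding one closed at 52 h and the session starts at 72 h. The same is true of a patient's first study session. If the bleed continues after the session, it also counts for the technique in use, and so may count twice.

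**Bleeding present at inclusion.** The endpoint requires neither new onset nor worsening. Such bleeding scores in every window while it persists, under A, B and C alike.

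**The case against.** The best reply is that this is loose wording with little practical effect. Several parts of it stand.

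- The spacing is not in the protocol. With even 56-hour spacing there is no overlap. If the 48 hours were meant to run from the session start, the session is covered and there is no overlap at 48-hour gaps.
- The Follow-up records are kept session by session: symptoms since the last session are taken when the next one starts, and clinical symptoms are noted during it. They may allow a bleed to be placed correctly. Section 9 also requires any adverse event observed during the research to be reported, so a bleed during dialysis need not vanish from the safety data.
- This is one secondary endpoint, and details of attribution are often left to a statistical analysis plan, which is not at hand.

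The last two do not remove the point. Section 7 states a window, and the stated window gives the wrong attribution; this is not a detail left open. No endpoint rule uses the session-level records to correct it.

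A reader might go further and infer three things that the documents do not support. First, that the definition makes adsorbed heparin look safer than it is. C can lose its own intradialytic bleeds, but its window also takes in bleeds during the A or B sessions that follow. The net direction depends on how much of any excess bleeding on C occurs during dialysis, and the protocol gives no such figure. Second, that every bleed on C in second or third position is charged to A or B. That needs triplets aligned with calendar weeks, which the protocol does not say; otherwise some of these bleeds are not counted at all. Third, that bleeding present at entry biases the comparison. Each patient is planned to receive all three techniques, so persistent bleeding dilutes the contrast and does not by itself favour one of them.

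**Conclusion.** The point holds as a defect in the definition of a secondary endpoint. The omission of the session's own 4 hours follows from the literal wording alone. The overlap with the next session rests on an assumed schedule: at 48/48/72 hours the whole next session is covered after two of three weekly sessions, at 46/50/72 hours the overlap is smaller, and at an even 56 hours it disappears. Where it occurs within a triplet, it always crosses techniques.

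The consequence is a blurred bleeding comparison, with some events counted for the preceding technique, some for none, and some diluted by bleeding already present. How many events are affected cannot be estimated from the protocol. The primary endpoint and the sample size are not touched. The change is worth making because it is small and the comparison of safety is a stated objective.

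**What to change.** Redefine the endpoint in section 7 as new or worsened bleeding from the start of session *n* to the start of session *n*+1, capped at 48 hours after the end of session *n*, attributed to the technique used in session *n*. Record bleeding present at the start of each session, and do not count it as an event unless it worsens. Name bleeding in both Follow-up records in section 5 (during the session and since the last session), so that the endpoint and the data collected for it agree.

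With this definition the session's own 4 hours are covered and the overlap is zero by construction. At 48/48/72 hours the windows last 48, 48 and 52 hours. The small difference in length goes with position in the week, and the six orders place each technique equally often in each position.

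The cost is one reworded endpoint sentence and one extra item on the case report form at the existing start-of-session assessment. No treatment, visit or sample size changes.

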**8- Data management and statistics**

***Justification of the number of patients to include***

The calculation of the number of subjects to include derives from the MacNemar test comparing groupes paired for a binary criteria:

|  | Response to treatment B | | | |
| --- | --- | --- | --- | --- |
| Response to the traitement of reference | Failure | Success | Total | Anticipated  Proportion |
| Failure | *r* | *s* | *r+s* | 1 - |
| Success | *t* | *u* | *t+u* |  |
| Total | *r+t* | *s+t* | Npaires |  |
| Anticipated  Proportion | 1 - |  |  |  |

This calculation is based on the estimation that =s/t measures the degree by which a patient will have a success with the reference treatement and a failure with treatment B, compared to failure with the reference treatement and success with treatment B. Of note, patients (*r+u*) having success-success or failure- failure are not taking into account in this calculation. The latter is based on anticipation of marginal probabilities of success, et , defined by the absence of circuit coagulation with each treatement:

- null hypothesis  : 70% in the reference treatment group (30% of clotting), group A,
- = 80% in the dilution group (20% of clotting), groupe B,
- = 90% int the AN 69 ST membrane (10% of clotting), group C,

thus estimating the proportion of discordant pairs :discordant = (*s+t*)/Npairs as well as values

Accoring to published tables, sample size tables for clinical studies, Blackwell Science, 1997 :

- number of pais
- to compare A and B with alpha=5% an a power of at least 80 %, values are for discordant = 0.38 et = 1,7, i.e 294 pairs of dialysis sessions.
- to compare A and C with alpha=5% and a power of 80 %, values are fordiscordant = 0.34 et = 3,85, i.e 65 pairs of dialysis sessions.
- In sum, at least 294 triplets of dialysis sessions are needed, i.e. 882 dialysis sessions, corresponding to 65 patients to recruit over 12 months.
- Each patient being a cluster of dialysis sessions patient, the number of dialysis sessions has to be increased according ta an inflation coefficient based on putative intra-class correlation ( 0.001 to 0.01) ; the inflation coefficient is estimated to range from 1,002 to 1,5 for a mean cluster of 6 dialysis sessions, i.e a raise from 884 sessions to 1323. We finally estimate the need to perform 1050 dialysis sessions in 75 different patients.

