**1- Summary**

Conventional hemodialysis requires systemic transient anticoagulation due to the activation of coagulation by contact between the patient's blood and the extracorporeal circuit. This anticoagulation, which uses heparin - fractionated or not – is however contra-indicated in patients with a high risk of bleeding. In this relatively common situation ( 10% of cases ), many procedures help perform hemodialysis without systemic anticoagulation, but no prospective study compare them. The reference method (" rinses " of the dialysis circuit with saline) is logistically cumbersome and subject to a relatively high failure rate. Two methods are emerging increasing use of : the continuous dilution of the dialysis circuit, and the exclusive anticoagulation the dialysis membrane by prior adsorption of heparin on a membrane having a treated non electronegative surface (NEPHRAL ST 400).

The single-center prospective randomized open controlled trial aims to compare " rinses ", " dilution " and " heparin adsorbed " in patients with a high risk of bleeding. The criteria will be clotting of the dialysis circuit (primary endpoint) and the efficacy and safety of dialysis ( secondary endpoints). This comparison will be made on the basis of statistics of randomized cross-over in unique individuals (" N- of- 1 trial ") series. We plan the inclusion of 78 different patients and implementation of 1050 dialysis without systemic heparinization.

We hope to show that, compared to " rinse " the " dilution " the " heparin adsorbed " technique reduces the frequency of coagulation circuit 30 and 50 %, respectively (primary endpoint) . We also hope to demonstrate that heparin adsorption allows ( i) better preservation of the porosity of the dialysis membranes, maintaining throughout the session a satisfactory removal of uremic waste, (ii) by limiting the use of fluids, helps to reach more often at the end of the session the dry weight of the patient and / or are to better clinically tolerate the dialysis sessions (secondary endpoints).

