***Mode of recruitment***

Monocentric study: patients treated by chronic hemodialysis at the Necker Hospital will be included. Given the number of sessions performed annually at our center (about 7500), the frequency of dialysis prescriptions without systemic anticoagulation (about 10% of cases) representing fifty patients a year to meet the inclusion criteria, we expected inclusion of a period of 18 months would be necessary.

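### The cluster-inflation factor of 1.002 to 1.5 does not follow from the stated ICC and cluster size, the cluster size contradicts the plan's own totals, and no route to 1050 sessions is shown

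*Protocol*

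**What the plan says.** The calculation is in Protocol section 8, under Justification of the number of patients to include. It has three steps.

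- **Base size.** The McNemar calculation for rinses (A) versus dilution (B) sets the size: "discordant = 0.38 et = 1,7, i.e 294 pairs of dialysis sessions". The comparison with adsorbed heparin (C) needs only 65 pairs. The conclusion is that "at least 294 triplets of dialysis sessions are needed, i.e. 882 dialysis sessions, corresponding to 65 patients".
- **Inflation.** Each patient is treated as a cluster of sessions, with a putative ICC of 0.001 to 0.01. Then "the inflation coefficient is estimated to range from 1,002 to 1,5 for a mean cluster of 6 dialysis sessions", which the protocol converts to 884 to 1323 sessions.
- **Target.** "We finally estimate the need to perform 1050 dialysis sessions in 75 different patients". No factor, ICC or reason is attached to the figure of 1050.

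Elsewhere, the Summary says "We plan the inclusion of 78 different patients and implementation of 1050 dialysis without systemic heparinization", and the section on the expected number of people also gives 78 and refers to the statistical section for the justification. The randomisation scheme in section 4 asks the trial to "make sure to have a number of patients included multiple of 6".

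**The concern.** The ICC, the cluster size and the factor appear in the same bullet, so the step can be checked directly, and it fails. The wide range 884 to 1323 comes entirely from a factor that the stated inputs cannot produce. The mean cluster of 6 cannot hold together with the number of patients and sessions planned. The chosen total lies between the two ends with no explanation.

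At stake is whether the target carries the power claimed for the comparison that sets the size. By the plan's own upper figure, 1323, the target is 273 sessions short. By its stated ICC, the target is enough. A reader cannot tell which was meant.

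**Working it through.** **Inputs.** From section 8: 294 pairs, 882 sessions, 65 patients, ICC 0.001 to 0.01, mean cluster 6, final target 1050 sessions in 75 patients, and clotting of 30% (A) and 20% (B). From Duration of participation: at most 12 triplets, that is 36 sessions per patient.

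**1. Base step.** Assuming independent responses, the discordant cells for A versus B are 0.30 × 0.80 = 0.24 and 0.70 × 0.20 = 0.14. Their sum is p = 0.38 and their ratio is ψ = 1.714. The McNemar formula is

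N = [z_α(ψ + 1) + z_β √((ψ + 1)² − (ψ − 1)²p)]² / [(ψ − 1)²p].

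At 5% two-sided (sidedness is not stated; two-sided fits best) and 80% power it gives 296 pairs, against 294 stated. With ψ rounded to 1.7 it gives 305. A versus C gives 65, as stated. The base step is sound.

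**2. Printed session range.** 882 × 1.002 = 883.8 and 882 × 1.5 = 1323. The session counts follow from the printed factors, so 1.5 was really used and is not a misprint of 1.05.

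**3. Factor from the stated inputs.** Design effect = 1 + (m − 1) × ICC, with sessions rounded up:

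| Cluster size m | ICC 0.001 | ICC 0.01 | Sessions from 882 |
|---|---|---|---|
| 6 sessions (stated) | 1.005 | 1.05 | 887 to 927 (886.4; 926.1) |
| 14 sessions (1050/75) | 1.013 | 1.13 | 894 to 997 (893.5; 996.7) |
| 4.67 triplets (350/75) | 1.004 | 1.037 | 886 to 915 (885.2; 914.3) |

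**4. What the printed factors would need.**

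- 1.002 at ICC 0.001 needs m = 1 + 0.002/0.001 = 3.
- 1.5 at m = 6 needs ICC = 0.5/5 = 0.1, ten times the stated upper bound.
- 1.5 at ICC 0.01 needs m = 1 + 0.5/0.01 = 51, above the 36-session maximum.
- No single m gives both ends. Counting 6 sessions as 2 triplets does not help: it gives 1.001 to 1.01.

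**5. Cluster size against the plan's totals.**

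- 1050/75 = 14.0; 1050/78 = 13.5; 882/65 = 13.6.
- Mode of recruitment puts about 10% of about 7500 annual sessions, so about 750, "representing fifty patients a year to meet the inclusion criteria". If all 750 belong to those fifty patients, that is 15 each.
- At 6 per patient, 75 patients give 450 sessions, and 1050 sessions need 1050/6 = 175 patients.

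**6. Route to 1050.** 1050/882 = 1.19. That needs ICC 0.19/5 = 0.038 at m = 6, or 0.19/13 = 0.0147 at m = 14. Both are outside the stated range.

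**7. Power on the plan's own upper factor.** 1050 sessions are 350 triplets, and 350/1.5 = 233.3 effective pairs. Solving the McNemar formula for power:

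z = [0.714 × √(233.3 × 0.38) − 1.96 × 2.714] / 2.678 = (6.726 − 5.320)/2.678 = 0.525, or about 70%.

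**8. Patient number.** 78 = 13 × 6. 75 is not a multiple of 6.

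**The case against.** The strongest reply is that the error may do no harm. The 80% power comes from the 294-pair step, which reproduces. Only the margin added on top is faulty. At the stated ICC, 1050 exceeds the corrected need at either cluster size (927 at 6, 997 at 14). In addition, every patient is meant to receive all three techniques, so a patient effect shared by all techniques largely cancels from the comparison, and a between-cluster factor is at best a rough guide. All of this stands. It limits the consequence but does not rescue the printed figures.

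A reader might go further in two ways, and the protocol supports neither.

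- **The trial is grossly underpowered.** One could take the ICC of 0.1 implied by 1.5 and combine it with 14 sessions per patient, for a factor of 2.3 and a much larger trial. But the protocol states 0.001 to 0.01, not 0.1, and a shared patient effect would not cost a within-patient comparison that much.
- **Unequal clusters make 1050 too few.** The Main Analysis section expects about 60% of patients to contribute 3 to 6 sessions and the rest to continue longer, so clusters will be unequal. It gives no distribution for the longer stays. If they are assumed to run from 18 to 36 sessions, the session-level formula at ICC 0.01 gives about 997 to 1158, and 1050 lies inside that range. The result depends on the assumed mix and on whether clusters are counted in sessions or triplets, so it is no evidence of a shortfall.

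The 75 versus 78 mismatch is separate from the inflation error. Rounding 75 up to the next multiple of 6 would explain it, but the protocol does not say so.

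**Conclusion.** The inflation step is wrong as written. With the stated ICC and cluster size the factor is 1.005 to 1.05, not 1.002 to 1.5. The cluster size of 6 is less than half the 13.5 to 14 sessions per patient that the plan's own totals imply. The target of 1050 is not derived from anything stated.

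The conclusion stops there. It is not shown that 1050 sessions are too few. With the stated ICC and equal clusters of 14, the requirement is 894 to 997. Only if the factor of 1.5 is taken at face value does power for A versus B fall to about 70%, below the stated aim of at least 80%. That figure rests on the plan's clotting rates, independent responses, a two-sided 5% test, and the plan's own practice of applying the factor to its session total.

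The discrepancies in factor, cluster size and patient number need no assumption beyond the standard design-effect formula, which is the only formula tried here that gives 1.5 at the stated cluster size (at ICC 0.1).

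**What to change.** Rewrite the last bullet of the sample-size justification so that it:

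1. states the intended ICC, and a cluster size and unit consistent with about 14 sessions (about 4.7 triplets) per patient;
2. recomputes the factor and session range from those inputs, and removes 1.5 and 1323 unless an ICC of 0.1 is really meant;
3. shows how 1050 is reached and restates the resulting power for A versus B;
4. notes that the between-cluster formula is only a rough guide here, because the techniques are compared within patient.

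Replace 75 with the patient number used in the Summary and in the section on the expected number of people (78, which meets the multiple-of-6 rule), or explain the difference.

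The choice of ICC belongs to the sponsor. If the stated range is kept, this is a text correction with no additional patients or sessions.
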